### Plans to promote participant retention and complete follow-up {18b}

The participants will receive extensive information about the study during the recruitment. The importance of completion of the follow-up will be stressed. However, the participants may voluntarily withdraw from the study for any reason at any time. We will use the application of CRDC to remind participants to follow-up regularly. They can also contact the study team if they have any questions of the study at any times.

For participants who fail to appear for study visits without stating an intention to withdraw, the study team will try to contact the participant through mobile device application, telephone calls, or short messages. If a participant withdrawal occurs for any reason, the study team must record the primary reason for a subject’s withdrawal from the study. If a participant withdraws from the study and disclosure of future information, no further evaluations will be performed, and no additional data will be collected. The investigator may retain and continue to use any data collected before such withdrawal of consent.

### Data management {19}

Data will be collected with electronic case report forms (eCRFs) and stored securely in the database of CRDC. Informed consent and signed paper forms will be stored within every center in a locked room with access granted only to authorized study staff. Source data will remain available in electronic patient record. All research data, including patient medical record, informed consent, and other related materials, will be archived for at least 5 years after the study.

### Confidentiality {27}

Research data including eCRFs will be stored securely into the database of CRDC. Access to the database will only be available to the research team during the study and will be documented and safeguarded by the principal investigator according to research guidelines after completion of the study. Other trial documents including the informed consent will be kept in locked cabinets. No participant identifying information will be disclosed in any publication or at any conference activities arising from the study.

### Plans for collection, laboratory evaluation, and storage of biological specimens for genetic or molecular analysis in this trial/future use {33}

As mentioned above, JAK/STAT pathway may take part in the process of pSS by affecting many cytokine signals. Because there are few studies about baricitinib in pSS, the exploration for the mechanism of JAK/STAT inhibitor in the treatment of pSS is important for further research. Therefore, we plan to collect the residue of blood and tissue specimens which were used for laboratory evaluation at every visit for further basic research such as genetic or molecular analysis in the future. Participants will be noticed and signed the informed consent.

## Statistical methods

### Statistical methods for primary and secondary outcomes {20a}

Data will be analyzed using IBM SPSS 23.0 (Chicago, IL, USA). Differences will be considered statistically significant if *p* < 0.05. Continuous variables were analyzed using paired *t*-tests for data comparison between the two treatment groups. Categorical variables were analyzed using the chi-square test or Fisher’s exact test, where appropriate. Two-tailed tests were used for all analyses, and *P* < 0.05 was considered statistically significant. The 95% confidence interval of the fixed effect size will be used to assess whether treatment difference reaches the minimally clinical important difference. The changes in outcome measures among all participants at 24 weeks will be used for intention-to-treat analyses.

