### Trial design {8}

This is a multi-center, prospective, open-label, randomized study to compare the efficacy of baricitinib + hydroxychloroquine (HCQ) with HCQ alone in pSS patients. Patients will be randomized (2:1) to receive baricitinib 4 mg per day + HCQ 400 mg per day or HCQ 400 mg per day alone. We will switch HCQ to baricitinib + HCQ if the patient in the latter group has no response at week 12. The final evaluation will be at week 24.

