#### Secondary outcome measure

Rate of MCII of ESSDAI at 24 weeks.Rate of EULAR pSS patient-reported index (ESSPRI) response, or MCII of ESSPRI, which was defined as an improvement of ESSPRI at least one point or 15%, at 12 and 24 weeks.Change of Physician’s Global Assessment (PGA) score from baseline at 12 and 24 weeks.Change of serological activity parameters including CRP, ESR, IgG, and RF levels from baseline at 12 and 12 weeks.Change of salivary glands function including the salivary flow rate (ml/min) and the Schirmer’s test (mm) from baseline at 12 and 24 weeks.Change of focus score on labial salivary gland biopsy [23] from baseline at 24 weeks. The minimum value is 1 and maximum value is 12, and higher scores mean a worse outcome.

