### Sample size {14}

According to the results of our pilot study [24] and clinical experiments, the expected response rate is 70% (μ) in baricitinib + HCQ group, and 30% (μ0) in HCQ group. We use this formula to calculate the sample size:$$N=\frac{{\left({z}_{a/2}+{z}_{\beta }\right)}^{2}{\sigma }^{2}}{{\left(\mu -{\mu }_{0}\right)}^{2}}$$

Zα/2 = 1.96 when alpha = 0.05, Zβ = 0.84 when beta = 0.2. After calculation, the sample will be 46:23. And consider the dropout rate as 20%, we will involve approximately 87 patients (58:29) for the study.

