## Assignment of interventions: allocation

### Sequence generation {16a}

Eligible participants will be randomized into HCQ group or baricitinib + HCQ group with a computer-generated randomization schedule operated at the application of CRDC.

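### The protocol assigns a paired t-test to the between-arm comparison of continuous secondary outcomes, but the arms are independent and unequal, so that test cannot make the comparison

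*Protocol article*

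**What the plan says.** Statistical methods {20a} gives one test for continuous variables: they are analysed "using paired *t*-tests for data comparison between the two treatment groups". The same paragraph assigns chi-square or Fisher's exact test to categorical variables. It also promises a 95% confidence interval for judging whether the treatment difference reaches a minimal important size, but names no model that would yield it. Additional analyses {20b} states that no adjusted analyses are planned.

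The design is parallel-group. Trial design {8} reads: "This is a multi-center, prospective, open-label, randomized study to compare the efficacy of baricitinib + hydroxychloroquine (HCQ) with HCQ alone in pSS patients", and "Patients will be randomized (2:1) to receive baricitinib 4 mg per day" plus HCQ, or HCQ alone. Allocation is made "with a computer-generated randomization schedule operated at the application of CRDC" (Sequence generation {16a}), and no matching is mentioned. Sample size {14} gives "After calculation, the sample will be 46:23" before dropout and then "we will involve approximately 87 patients (58:29) for the study".

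The secondary outcomes include continuous changes, for example "Change of Physician’s Global Assessment (PGA) score from baseline at 12 and 24 weeks". The others are the serological parameters, salivary flow, Schirmer's test and, at week 24 only, the focus score.

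**The concern.** The sentence names a test and a purpose that do not fit together. A paired t-test analyses differences within linked pairs. A patient on baricitinib + HCQ has no partner in the HCQ arm, and the arms are not the same size. Whoever runs the analysis must therefore depart from the text, and there are three ways to do so:

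- Read paired as a slip for unpaired. This gives a valid test.
- Pair patients arbitrarily. This leaves out half of the larger arm and makes the result depend on who is matched with whom.
- Run a before/after test in each arm and compare the two verdicts. This does not estimate or test a treatment difference.

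The third is the one to guard against, because change from baseline is what a paired t-test naturally handles. Some change shared by both arms is plausible here. Entry requires active disease (ESSDAI of at least 5) and abnormal serology, several of those serological measures are then outcomes, and the trial is open-label. Shared change can appear as significant in one arm and not in the other when the drug adds nothing.

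**Working it through.** **Inputs.** Arm sizes are 46 and 23 evaluable, 58 and 29 enrolled (Sample size {14}). Tests are two-sided at 0.05 ({14}, {20a}). The document gives no SD or expected change for any continuous outcome, so effect sizes below are in SD units and are assumptions.

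**Arm sizes.** The dropout step reproduces: 46/0.8 = 57.5, rounded up to 58; 23/0.8 = 28.75, rounded up to 29; total 87.

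**Can the stated test be run between arms?** No. A paired routine given 58 and 29 values fails because the lengths differ. Arbitrary pairing could use at most 29 of the 58 baricitinib patients. In simulation (20,000 trials, 58:29, true difference 0.65 SD) it had 67% power, against 81% for an independent t-test on all patients.

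**What happens if it is run within each arm?** Let d be the true mean change divided by the SD of change, the same in both arms, so the drug adds nothing. The power of a before/after t-test with n patients is

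P(n, d) = Pr(|T| > t), where T is noncentral t with n − 1 degrees of freedom and noncentrality d√n, and t is the 97.5% point of central t.

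The arms are independent, so the chance that baricitinib is significant and HCQ is not equals P(46, d) × [1 − P(23, d)]:

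| d | P(46, d) | P(23, d) | Baricitinib significant, HCQ not |
|---|---|---|---|
| 0 | 5% | 5% | 4.8% |
| 0.1 | 10% | 7% | 9% |
| 0.2 | 26% | 15% | 22% |
| 0.385 | 72% | 42% | 42% (maximum) |
| 0.6 | 98% | 79% | 21% |
| 0.8 | >99% | 96% | 4% |
| 1.0 | >99% | >99% | 0.4% |

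At 58:29 the maximum is 41.5%, at d = 0.34. Simulation at 58:29 gave 26%, 40%, 39%, 25% and 12% at d = 0.2, 0.3, 0.4, 0.5 and 0.6. In the same simulated data an independent-samples t-test rejected in 4.7% to 5.1% of trials.

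**Is the 2:1 ratio the cause?** Only in part. With equal arms of 34 and 34, the same discordance is still 24% at d from 0.3 to 0.385. Comparing two significance verdicts is the main fault, and unequal arms make it worse.

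**What the corrected test can detect.** With 80% power (normal approximation), the detectable difference is (1.96 + 0.84) × √(1/58 + 1/29) = 0.64 SD at 58:29, and (1.96 + 0.84) × √(1/46 + 1/23) = 0.72 SD at 46:23.

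**The case against.** The strongest reply is that this is a wording slip. The sentence says the comparison is between groups, and the later promise of a confidence interval for the treatment difference shows that a between-arm estimate was intended. On that reading, correcting one word removes the harm. This is plausible, and it limits how serious the point is. It does not remove the point, because the text names the wrong test, offers no other for continuous outcomes, and attaches no method to the interval. A separate analysis plan could supply detail that is missing here, but this sentence is an incorrect statement and not a gap.

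A second reply is that the 42% belongs to a procedure that the protocol does not describe. That is right. It is a peak over assumed effect sizes under one possible workaround. Outside a middle band of shared change the figure is close to or below 5%, so it should be given only as part of the range.

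A reader might also infer that the trial's main result is at risk. The documents do not support this. The primary endpoint is a response rate at week 12, the ESSDAI and ESSPRI responses are also rates, and all of them fall under chi-square or Fisher's exact test. The sample size rests on response rates too.

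**Conclusion.** The point holds for the continuous secondary outcomes only: PGA, CRP, ESR, IgG, RF, salivary flow, Schirmer's test and focus score. For these, the stated between-arm test cannot be run on independent arms of 58 and 29, and no other section names a valid one.

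The consequence depends on the workaround. It is nil if the analyst simply uses an unpaired test. Arbitrary pairing costs power, from 81% to 67% at an assumed 0.65 SD. Within-arm tests read against each other give a misleading contrast with probability from about 5% (no change) up to about 42% (d = 0.385), falling to about 4% at d = 0.8, for 46 v 23. These figures assume normally distributed changes, the same standardised change in both arms, and effect sizes that the document does not supply. The 42% is not an expected error rate for this trial.

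**What to change.** In section {20a}, replace the paired t-test sentence with wording to this effect:

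> Change from baseline in each continuous outcome is compared between the randomised arms with an independent-samples (Welch) t-test at every time point listed for that outcome, and reported as a mean difference with 95% CI. Paired t-tests are used only to describe change within an arm.

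The time points should follow the secondary outcome list: weeks 12 and 24 for PGA, salivary flow and Schirmer's test, and week 24 alone for the focus score. A rule confined to week 12 would leave the focus score with no analysis. The serology entry prints week 12 twice, while the participant timeline shows these tests at weeks 12 and 24, so that entry should be settled in the same edit.

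Preferably, use ANCOVA with the baseline value as covariate and report the adjusted mean difference with 95% CI. In that case section {20b}, which rules out adjusted analyses, must be amended to match. The Welch option needs no such change.

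Week-24 comparisons should be by randomised arm. They should be read in the light of the week-12 switch, after which HCQ non-responders also receive baricitinib.

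The cost is one sentence, or two edits with ANCOVA. No new data are needed, both methods are available in the stated software, and the planned 87 patients do not change because the sample size is set by the binary primary endpoint.

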**Methods:**

This is a multi-center, prospective, open-label, randomized study to compare the efficacy of baricitinib + hydroxychloroquine (HCQ) with HCQ alone in pSS patients. We plan to involve 87 active pSS patients with European League Against Rheumatism pSS disease activity index (ESSDAI) ≥ 5 from eight different tertiary centers in China. Patients will be randomized (2:1) to receive baricitinib 4 mg per day + HCQ 400 mg per day or HCQ 400 mg per day alone. We will switch HCQ to baricitinib + HCQ if the patient in the latter group has no ESSDAI response at week 12. The final evaluation will be at week 24. The primary endpoint is the percentage of ESSDAI response, or minimal clinically important improvement (MCII), which was defined as an improvement of ESSDAI at least three points at week 12. The secondary endpoints include EULAR pSS patient-reported index (ESSPRI) response, change of Physician’s Global Assessment (PGA) score, serological activity parameters, salivary gland function test, and focus score on labial salivary gland biopsy.

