### Objectives {7}

We hope to provide reliable evidence of baricitinib as a new potential oral therapy for pSS. The primary endpoint is the percentage of European League Against Rheumatism (EULAR) pSS disease activity index (ESSDAI) response, or minimal clinically important improvement (MCII), which was defined as an improvement of ESSDAI at least three points [18], at 12 weeks.

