### Outcomes {12}

#### Primary outcome measure

The rate of ESSDAI response, or MCII of ESSDAI, which was defined as an improvement of ESSDAI at least three points, at 12 weeks.

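### The P < 0.05 significance rule covers every analysis, so each of 14 (or 18) secondary tests can be declared significant at full alpha even if the primary fails

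*Protocol article*

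**What the plan says.** The protocol article names one primary outcome at one time: "The rate of ESSDAI response, or MCII of ESSDAI, which was defined as an improvement of ESSDAI at least three points, at 12 weeks". All other efficacy measures stand in a separate, unranked list under the secondary outcome heading.

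Section {20a}, whose heading covers both primary and secondary outcomes, gives the significance rule twice. The first statement is "Differences will be considered statistically significant if *p* < 0.05". The second is broader: "Two-tailed tests were used for all analyses, and *P* < 0.05 was considered statistically significant". Neither is limited to the primary outcome. The same section also says that a 95% confidence interval will be compared with the minimal clinically important difference. Section {20b} excludes subgroup and adjusted analyses, so these add no tests.

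The serology entry reads "Change of serological activity parameters including CRP, ESR, IgG, and RF levels from baseline" and then gives week 12 twice as its time points. Table 2 schedules acute phase reactants and immunological parameters at both week 12 and week 24.

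**The concern.** The secondary outcomes fall under a rule that the article states outright. Applied as written, a single CRP or Schirmer result at P = 0.04 is statistically significant by the protocol's own definition, even when the week-12 ESSDAI comparison is not. With 14 or more such tests, some result of this kind is fairly likely by chance alone.

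The stated hope is "We hope to provide reliable evidence of baricitinib as a new potential oral therapy for pSS". The trial plans 87 patients and is open-label. After a null primary, an isolated secondary result described in the protocol's own terms as significant could be read as evidence of efficacy, and a reader could not tell it from a controlled finding.

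**Working it through.** **Plan's own figure.** The article states no familywise error rate, so there is none to reproduce.

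**Counting the secondary tests** (Outcomes {12}, secondary list):

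| Outcome | Time points | Tests |
|---|---|---|
| ESSDAI response | week 24 | 1 |
| ESSPRI response | weeks 12, 24 | 2 |
| PGA change | weeks 12, 24 | 2 |
| CRP, ESR, IgG, RF change | week 12 as printed; weeks 12 and 24 per Table 2 | 4 or 8 |
| Salivary flow, Schirmer's test | weeks 12, 24 | 4 |
| Focus score | week 24 | 1 |

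As printed: 1 + 2 + 2 + 4 + 4 + 1 = 14. With serology at both visits: 1 + 2 + 2 + 8 + 4 + 1 = 18.

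**Inputs.** Each test is two-sided at 0.05 (section {20a}), so the critical value is c = 1.96. The null is that baricitinib has no effect on any outcome. The correlation ρ between test statistics is not in the documents. It is assumed equal across all pairs and varied.

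**Any false significant secondary result, in either direction.**

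- Independent tests: 1 − 0.95^14 = 0.512 and 1 − 0.95^18 = 0.603.
- Common correlation ρ: 1 − ∫ [U(u) − L(u)]^k φ(u) du, where U(u) = Φ((c − √ρ·u)/√(1−ρ)), L(u) = Φ((−c − √ρ·u)/√(1−ρ)), and k is the number of tests.

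**The harm described above:** the primary is not significant and at least one secondary is significant in favour of baricitinib. With the primary given the same correlation, this is ∫ [U(u) − L(u)]·[1 − U(u)^k] φ(u) du.

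| ρ (assumed) | Any false secondary, k = 14 / 18 | Primary not significant and a secondary favours baricitinib, k = 14 / 18 |
|---|---|---|
| 0 | 51.2% / 60.3% | 28.4% / 34.8% |
| 0.2 | 47.5% / 55.5% | 23.5% / 27.9% |
| 0.5 | 34.8% / 39.8% | 15.6% / 18.0% |
| 0.8 | 19.7% / 21.6% | 7.6% / 8.5% |

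The ρ = 0 entries in the last column are 0.95 × (1 − 0.975^14) = 0.284 and 0.95 × (1 − 0.975^18) = 0.348.

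**Sensitivity to the correlation pattern.** If the same measure at weeks 12 and 24 is correlated 0.7 and different measures 0.2, simulation gives 45.1% (14 tests) and 51.6% (18 tests) for any false secondary result. This lies inside the range above.

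**Limit of the calculation.** Three of the tests are on response rates, for which section {20a} names chi-square or Fisher's exact tests. The other 11 (14 − 3) or 15 (18 − 3) are on continuous changes, for which it names paired t-tests between two separate groups. A true 5% error rate per test is therefore assumed here and is not assured by the plan.

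**The case against.** The strongest objection is that handling of multiplicity among secondary outcomes is commonly left to the statistical analysis plan, which is not shown, and that a journal article condenses. A conventional 0.05 sentence need not be a decision against any hierarchy. The outcomes are plainly labelled secondary, one primary is fixed, and section {20a} also relies on a confidence interval. This stands to the extent that the absence of a multiplicity scheme is no finding. It does not dispose of the point, because section {20a} positively applies the significance label to all analyses, under a heading that includes secondary outcomes. An analysis plan that withheld the label from secondary results would have to depart from that sentence.

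The second objection concerns size. A reader might infer a flat 35–40% chance of a spurious benefit. The documents do not support that figure. It needs an assumed correlation of 0.5, it counts results in both directions (at that correlation about half favour HCQ alone), and it takes no account of whether the primary succeeds. The probability that matches the harm is about 16–18% at the same correlation.

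A reader might also infer that the trial's main conclusion is compromised. It is not on this ground: there is one primary comparison at one time point, with its own 0.05.

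Finally, the background describes the study as exploring efficacy and safety. That describes the study as a whole and does not mark the secondary tests as exploratory.

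**Conclusion.** The point holds as a fault in a stated rule. As written, any of the 14 secondary tests (18 if serology is also tested at week 24) may be declared statistically significant at full alpha regardless of the primary result.

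If baricitinib has no effect, the chance of at least one false significant secondary result is about 51–60% under independence, 35–40% at correlation 0.5 and 20–22% at 0.8. The lower end is still about four times 5%. The chance of a non-significant primary together with a secondary falsely favouring baricitinib is about 16–18% at correlation 0.5, and about 8–28% over correlations 0.8 to 0.2.

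All of these figures rest on assumed correlations, on no effect on any outcome, and on a true 5% error per test. The fault limits what may be claimed from secondary outcomes. It does not touch the primary test.

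**What to change.** In section {20a}, restrict the statement that P < 0.05 is statistically significant to ESSDAI response at week 12. Add that secondary outcomes are reported as between-arm estimates with 95% confidence intervals and nominal p-values, without claims of significance.

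An optional alternative is a short fixed sequence of secondary outcomes, tested at two-sided 0.05 only after a significant primary and stopping at the first non-significant result. The sponsor would choose the order, and everything outside the sequence would be reported as above.

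In the secondary outcome list, correct the serology entry that gives week 12 twice, so that the set of secondary comparisons is defined.

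The cost is a few sentences. No patients, visits or data are added and the primary loses no power. The downside is that isolated secondary results can no longer be called statistically significant.

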### Intervention description {11a}

Patients with active pSS (ESSDAI ≥ 5) under 12 weeks treatment of HCQ will be involved in the study. Patients will be randomized (2:1) to receive baricitinib 4 mg per day + HCQ 400 mg per day or HCQ 400 mg per day alone. Patients will come to visit at weeks 0, 4, 8, 12, 16, 20, and 24. Patients who have no ESSDAI response to HCQ treatment alone at week 12 will be switched to baricitinib + HCQ group and added on with baricitinib 4 mg per day until the end of the study (week 24). The final evaluation will be at week 24.

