### Interim analyses {21b}

Patients who have no ESSDAI response to HCQ treatment alone at week 12 will be switched to baricitinib + HCQ group and added on with baricitinib 4 mg per day until the end of the study (week 24). There are no interim safety analyses planned for this trial.

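### Intention-to-treat is attached only to week 24, after control non-responders have started baricitinib; it belongs on the week-12 primary endpoint, and week 24 needs its own label

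*Protocol article*

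**What the plan says.** All references are to the protocol article.

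- **Primary outcome measure:** the endpoint is given as "The rate of ESSDAI response, or MCII of ESSDAI, which was defined as an improvement of ESSDAI at least three points, at 12 weeks".
- **Intervention description {11a}:** "Patients who have no ESSDAI response to HCQ treatment alone at week 12 will be switched to baricitinib + HCQ group", with baricitinib then added until week 24. Interim analyses {21b} repeats the rule. Trial design {8} gives it as a change of treatment, without the word group.
- **Secondary outcome measure:** the first item is "Rate of MCII of ESSDAI at 24 weeks". ESSPRI response, PGA and gland function are listed at both 12 and 24 weeks. "Change of focus score on labial salivary gland biopsy" is listed at 24 weeks only, and Table 2 schedules the biopsy at screening and week 24 alone.
- **Statistical methods {20a}:** "The changes in outcome measures among all participants at 24 weeks will be used for intention-to-treat analyses". No other sentence in the article mentions intention-to-treat.
- **Sample size {14}:** "the expected response rate is 70% (μ) in baricitinib + HCQ group, and 30% (μ0) in HCQ group", leading to 46:23 evaluable and 58:29 enrolled.
- **Methods for additional analyses {20b}:** no adjusted or subgroup analyses are planned.

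**The concern.** The stated aim is to compare baricitinib + HCQ with HCQ alone. The intention-to-treat label sits on the visit where that contrast no longer exists, and not on the visit where it does. After week 12 every control still on HCQ alone is a week-12 responder, and the other controls have had 12 weeks of baricitinib. The switch depends on outcome and happens in one arm only, so it pulls the arms together, and more strongly the better the drug works in those who switch.

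If the sentence is followed, a week-24 comparison could be reported as the intention-to-treat result and read as evidence for or against baricitinib over HCQ alone, when it estimates something else. Focus score is the most exposed, because it has no pre-switch comparison to fall back on.

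**Working it through.** **Timing.** The primary endpoint is read at week 12. Table 2 marks the same visit as the switch checkpoint, and the switch is decided by that ESSDAI result, so the week-12 response is measured before any control takes baricitinib. The intention-to-treat sentence refers to a visit 12 weeks later.

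**The plan's own figures.** Dropout step: 46/0.8 = 57.5, rounded up to 58; 23/0.8 = 28.75, rounded up to 29. This agrees with the 58:29 stated. At week 12 the difference is 0.70 - 0.30 = +40 points. With the formula below, power is 90% at 46:23 and 96% at 58:29. (The plan states 80%. That mismatch is a separate matter and nothing here depends on it.)

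**Controls expected to switch.** 1 - 0.30 = 0.70 of the arm: 0.70 × 29 = 20.3 enrolled, or 0.70 × 23 = 16.1 evaluable.

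**Week-24 difference by randomised arm.** Let

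- r = response at week 24 among switched controls,
- k = share of week-12 HCQ responders still responding at week 24,
- p_B = week-24 response in the baricitinib arm.

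The protocol gives none of these three; all are assumptions. Then

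p_H = 0.30k + 0.70r, and D = p_B - p_H.

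Power in favour of baricitinib (two-sided 5%, n = 46:23) is Φ[(D - 1.96·s0)/s1], where

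- p̄ = (23·p_H + 46·p_B)/69,
- s0 = √[p̄(1 - p̄)(1/23 + 1/46)],
- s1 = √[p_H(1 - p_H)/23 + p_B(1 - p_B)/46].

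Example with p_B = 0.70, k = 1, r = 0.30: p_H = 0.30 + 0.21 = 0.51; D = 0.19; p̄ = 0.637; s0 = 0.123; s1 = 0.124. (0.19 - 1.96 × 0.123)/0.124 ≈ -0.41, so power is 34%.

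| p_B | k | r = 30% | r = 50% | r = 70% |
|---|---|---|---|---|
| 70% | 100% | +19 (34%) | +5 (6%) | -9 (0.2%) |
| 80% | 100% | +29 (70%) | +15 (28%) | +1 (3%) |
| 70% | 80% | +25 (52%) | +11 (15%) | -3 (1%) |
| 80% | 80% | +35 (84%) | +21 (46%) | +7 (10%) |

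Cells show the difference in percentage points, with power in favour of baricitinib in brackets.

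**What the switch itself removes.** If non-responding controls would have gained nothing by staying on HCQ alone, the switch takes 0.70 × r off the difference: 21 points at r = 30% and 49 points at r = 70%. If some would have responded late on HCQ alone, the loss is smaller by 0.70 times that rate.

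**How much rests on the baricitinib arm.** Holding it at 70% assumes that none of its week-12 non-responders improves in 12 more weeks on the drug. If 30% of them do, p_B = 0.70 + 0.30 × 0.30 = 79%. With k = 1, D is then 0 at r = 70%. At r = 35%, p_H = 0.30 + 0.245 = 54.5% and D = +24.5 points. Exact chi-square power for that last case at 58:29 is 0.67, against 0.31 with the arm held at 70%.

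**The case against.** The best defence is that the primary comparison is untouched. Week-12 ESSDAI response precedes the switch, and ESSPRI, PGA and gland function also have week-12 assessments. Only week-24 secondary results are affected, and focus score alone lacks an earlier reading. This stands. A reader might infer that the trial cannot show the drug's effect; the documents do not support that. It can do so at week 12, and at week 24 the effect of immediate over deferred start remains estimable.

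Second, the primary analysis population and the handling of switched patients are often left to an analysis plan, which is not at hand. That also stands, so their absence is not the point here. The point is a sentence that is present and attaches intention-to-treat to the wrong visit.

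Third, a reader might infer from the word group in "Patients who have no ESSDAI response to HCQ treatment alone at week 12 will be switched to baricitinib + HCQ group" that switched controls will be counted in the baricitinib arm. That would break randomisation and leave only about 9 controls (0.30 × 29 = 8.7), all week-12 responders. The protocol does not say so. Other sections describe only a change of treatment, and intention-to-treat ordinarily means by randomised arm. The wording is worth clearing up, but it is not evidence of such an analysis.

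Fourth, a reversal in which HCQ looks better at week 24 appears in the table only with the baricitinib arm held at 70% and high response among switched patients. At 80% the difference stays positive throughout. Dilution is well supported; reversal is possible but depends on the assumptions.

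**Conclusion.** The sentence is wrong as written and should be corrected. It puts intention-to-treat on a visit after an outcome-driven, one-way switch expected in about 70% of controls (20 of 29), and leaves it off the primary endpoint. By randomised arm, week 24 estimates immediate versus deferred, non-response-triggered baricitinib.

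With all HCQ week-12 responses maintained, switched-patient response of 30% to 70% and a baricitinib arm of 70% to 80%, the planned +40 points becomes about +29 to -9. If only 80% of HCQ responses are maintained, the range is +35 to -3. Every scenario shown lies below +40, but the exact size cannot be fixed from the protocol.

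The problem affects secondary endpoints and the label of the primary analysis population, not the validity of the week-12 comparison. It does not call for a ban on week-24 between-arm comparisons: a comparison by randomised arm is valid for what it estimates, provided it is labelled so.

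**What to change.** 1. In Statistical methods {20a}, replace the sentence with: *The intention-to-treat analysis of the primary endpoint includes all randomised patients, by randomised arm, at week 12.*
2. State that controls who switch stay in the HCQ arm in all between-arm analyses. Make clear in Intervention description {11a} and Interim analyses {21b} that the switch describes treatment and not analysis group.
3. Label every week-24 between-arm result, including focus score, as immediate versus deferred start: supportive only, and not evidence for or against the effect over HCQ alone. Describe switched patients separately as well.

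This needs wording in the analysis section and a clarification in two others. No visit, treatment rule or sample size changes. The real cost is that week-24 endpoints, and focus score entirely, no longer support a claim against HCQ alone.
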